#### Data collection, access, and management

3.8.6

All information regarding the patient is anonymized through initial processing, and all investigators are obliged to maintain confidentiality of the results. The source document is registered immediately when the data are collected, and it will be recorded in the CRF. All the documents of trial will be kept safe, and only those who have been approved by the principal investigator will have access to all data related with the trial.

Data management of this clinical trial will be conducted in accordance with the standard working guidelines of the Catholic Kwandong University Clinical Research Center, and other matters not specified in the protocol will be conducted following the International Council for Harmonisation of Technical Requirements for Pharmaceuticals for Human Use (ICH) guideline for GCP and Korea-GCP standards.

### Statistical analysis

3.9

All statistical analyses will be conducted by a blinded professional statistician. All participants who provided written consent and were assigned a screening number for the study are included in the screening set, and patients randomized to the treatment group are included in the randomized set. Intention-to-treat (ITT) analysis will be performed in patients who have received at least one pregabalin trial or at least one session of acupuncture or CMT. Per-Protocol Set (PPS) analysis will be performed in patients who meet the inclusion/exclusion criteria, have no significant conditions affecting the efficacy assessment, show > 80% treatment compliance, and have performed at least one evaluation after the baseline evaluation.

The statistical analysis for the efficacy evaluation, based on ITT analysis and PPS analysis are conducted in parallel. All statistical tests will be performed as two-sided tests with a significance level of 5%, and two-sided 95% confidence intervals. Primary outcome assessments are performed with ANOVA analysis to test the differences between the groups for changes in FACT/GOG-NTX at the end of week 5, compared to baseline. If the differences between groups are significant, the Tukey method will be used. For secondary outcome evaluation, continuous variables are analyzed with ANOVA analysis or Kruskal–Wallis test, and categorical variables are analyzed with Pearson's chi-squares test or Fisher's exact test. The Exploratory Efficacy assessment will summarize the descriptive statistics on the chemotherapy completion rate, followed by the appropriate statistical analysis.

For the occurrence of adverse events, the number of cases, number of participants, severity, and causal relationship with the investigational drug can be statistically analyzed by group, and nonparametric methods can be applied as needed. The results of vital signs, physical examination, electrocardiograms, and laboratory tests will be reviewed in a comprehensive manner, and statistical analysis will be conducted as necessary for the test items deemed clinically significant by the investigators. Depending on the nature of the data, continuous data will be summarized by observed values, mean, standard deviation, median, minimum, and maximum for each visit, and categorical variables will be summarized by frequency and percentage.

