#### Chuna manual therapy group

3.4.3

The CMT group is treated with CMT, in addition to conventional therapy. In Chuna treatment, patients with colorectal cancer lie down on their side and Sunwoo manual therapy, which helps joint movement and improves overall function is used.^[19]^ Sunwoo manual therapy may cause unnecessary irritation to the area affected by breast cancer. Thus, CMT for meridian sinew system, which is applied to the nerves of the ribs, upper and lower limbs is utilized. CMT is conducted twice a week for the first 2 weeks and once a week for the following 3 weeks.

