### Recruitment, randomization, blinding and non-blinding

3.6

Advertisements for patient recruitment will be posted on the Catholic Kwandong University International St. Mary's Hospital bulletin boards, along with posters, banner advertisements and internet cafes. All advertisements will be run after IRB approval.

Individuals who have given written consent for participating in the study will be assigned a screening number, in order of the outpatient visit at screening. Unblinded sub-investigators, who do not influence the research results and analysis, will refer to the randomization list that has been prepared by a commissioned professional statistician, and assign participation numbers by stratification (based on the presence of breast cancer or colorectal cancer). The randomized list will be generated by layer considering the stratification factor by the block randomization method, and participants will be allocated to the pregabalin group, the pregabalin + EA group, and the pregabalin + CMT group in a ratio of 1: 1: 1. A randomization table is generated by an independent statistician and patients are assigned to one of three groups according to the randomization table. Screening numbers, randomization numbers, and initials assigned to each participant are used as subject identification codes to identify the participant until the end of the clinical trial.

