#### Primary outcome

3.8.1

The primary outcome in this study measures the changes in the Functional Assessment of Cancer Therapy/Gynecologic Oncology Group Neurotoxicity (FACT/GOG-Ntx) subscale (version 4.0, Korean) in comparison with the baseline, in which scores from 11 questions, each consisting of 0 to 4 points will be evaluated. A higher score indicates a more severe degree of peripheral neuropathy.^[20,21]^ The FACT/GOG-NTX questionnaire is to be self-administered by the participants.

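### The primary ANOVA of change leaves out the baseline score as a covariate and the cancer-type stratum; it is valid but gives up precision that an ANCOVA would recover at no cost

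*Protocol article*

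**What the plan says.** Section 3.9 of the protocol article fixes the primary test: "Primary outcome assessments are performed with ANOVA analysis to test the differences between the groups for changes in FACT/GOG-NTX", evaluated "at the end of week 5, compared to baseline". If the overall test is significant, Tukey comparisons follow. The level is two-sided 5%, with 95% confidence intervals. No covariate and no stratum term is named.

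Section 3.8.1 defines the outcome as the change "in comparison with the baseline, in which scores from 11 questions, each consisting of 0 to 4 points will be evaluated", so a baseline score is needed for every patient who enters the primary analysis.

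Section 3.6 has sub-investigators "assign participation numbers by stratification (based on the presence of breast cancer or colorectal cancer"), and adds: "The randomized list will be generated by layer considering the stratification factor by the block randomization method". Allocation is 1:1:1.

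Section 3.3 sets 30 patients per group and 90 in total, by comparison with earlier studies of about 20 per group, and allows for 20% dropout. It calls the trial a pilot and gives no effect size, SD or power.

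**The concern.** Subtracting the baseline score fixes its regression slope at 1. When the best-fitting slope is below 1, change is negatively correlated with baseline, and chance baseline differences between arms add noise to the contrasts. ANCOVA estimates the slope and removes that noise.

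The stratified design balances the arms on cancer type, but a one-way ANOVA leaves any variation between strata in its error term. If the two cancers differ in mean change, the computed standard errors exceed the true sampling variation. A difference is plausible, because the stratum determines the causative drug (oxaliplatin or a taxane, section 3.5.1) and, in the CMT arm, the technique (section 3.4.3). The document does not quantify it.

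What is at stake is power and interval width, in a trial with 24 to 30 patients per arm that tests a superiority hypothesis (section 2) at 5%.

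**Working it through.** **The plan's own figures.** 3 × 30 = 90, and 30 × (1 − 0.20) = 24 per arm, which is above 20. These reproduce. No power is stated, so there is none to reproduce.

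**Inputs from the document.** Three arms, 1:1:1; 30 per arm, or 24 after dropout; two-sided 5%; Tukey.

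**Assumptions, because the document gives no figures.**
- Correlation rho between baseline and week-5 score: 0.3, 0.5 or 0.7.
- Ratio k of baseline SD to week-5 SD: 1 or lower.
- True pairwise difference: 0.6 SD of the raw score.
- Gap in mean change between the two cancers: 0, 0.5 or 1.0 SD of the raw score.
- Split of patients by cancer: 48/42, in permuted blocks of 6.

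**Step 1: baseline adjustment.** In units of the week-5 variance, per patient:
- change score: k² + 1 − 2·rho·k
- ANCOVA: 1 − rho²

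The difference is (k − rho)², which is never negative, so apart from the degree of freedom spent ANCOVA does not lose. With k = 1 the ratio of ANCOVA to change score is (1 − rho²) / [2(1 − rho)] = (1 + rho)/2.

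| rho | change | ANCOVA | ratio, k = 1 | CI narrower by | ratio, k = 0.8 | CI narrower by |
|---|---|---|---|---|---|---|
| 0.3 | 1.40 | 0.91 | 0.65 | 19% | 0.91/1.16 = 0.78 | 11% |
| 0.5 | 1.00 | 0.75 | 0.75 | 13% | 0.75/0.84 = 0.89 | 6% |
| 0.7 | 0.60 | 0.51 | 0.85 | 8% | 0.51/0.52 = 0.98 | 1% |

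The change and ANCOVA columns are for k = 1. CI narrowing is 1 − √ratio. At k = 0.7 and rho = 0.7 the true slope rho/k equals 1, the ratio is 1.00 and there is no gain.

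**Step 2: power of one pairwise comparison.** With n = 24 per arm, k = 1 and variance v from step 1, the standard error is √(2v/24) and the noncentrality is 0.6 divided by it. The Tukey critical value for three groups and 69 df is 2.40. Power comes from the noncentral t, without the requirement that the overall test is significant first.

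| rho | noncentrality, change | power | noncentrality, ANCOVA | power |
|---|---|---|---|---|
| 0.3 | 0.6/0.342 = 1.76 | 27% | 0.6/0.275 = 2.18 | 42% |
| 0.5 | 0.6/0.289 = 2.08 | 38% | 0.6/0.250 = 2.40 | 50% |
| 0.7 | 0.6/0.224 = 2.68 | 61% | 0.6/0.206 = 2.91 | 70% |

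**Step 3: the stratum.** Simulation with 4,000 trials per scenario, 90 patients, rho = 0.5 and k = 1. The table shows the change-score ANOVA without the stratum under no treatment effect.

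| gap in mean change | mean model SE / empirical SE | coverage of 95% CI | type I error |
|---|---|---|---|
| 0 | 1.00 | 95.2% | 5.1% |
| 0.5 SD | 1.02 | 95.4% | 4.9% |
| 1.0 SD | 1.12 | 97.2% | 2.8% |

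A direct formula agrees closely. The between-stratum variance is gap² × (48/90)(42/90), and the SE inflates by √(1 + that/v). With v = 1 this gives √1.062 = 1.03 for 0.5 SD and √1.249 = 1.12 for 1.0 SD. At rho = 0.7 with a 0.5 SD gap the simulated ratio is about 1.05.

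Adding the stratum restores coverage to about 95%. Baseline alone is not enough: at a 1.0 SD gap, ANCOVA on baseline without the stratum has an SE ratio of 1.16 and a type I error of 1.8%, while ANCOVA with both terms gives 1.00 and 4.8%. No scenario showed inflated type I error or under-coverage for the unadjusted analysis.

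**The case against.** A change-score ANOVA in a randomised trial is conventional, unbiased and controls type I error. The trial calls itself a pilot and has no power target to miss. The gain rests on a correlation and an SD ratio that the document does not give. Entry requires CTCAE grade 2 or higher at screening (section 3.5.1), which may narrow the baseline spread and bring the gain close to nothing at high correlation. The unseen analysis plan may also add covariates, and an ANOVA that includes a stratum factor is still an ANOVA.

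Much of this stands. It limits the point to efficiency and requires the gain to be given as a range. It does not remove the point: the article does name its primary model, the named model lacks both terms, and adding them carries no appreciable loss under any of the assumptions.

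A reader might infer four stronger things that the document does not support.
- That the baseline is ignored: it is subtracted; only regression adjustment is missing.
- That the arm contrasts are distorted: under randomisation, chance baseline imbalance adds variance, not bias, and that variance is already counted in step 1.
- That the error bars are wrong: they are correct if cancer type does not predict change, and too wide, hence conservative, if it does.
- That no estimates by cancer type are planned: such summaries are ordinary analysis-plan content, so a condensed article that omits them shows nothing. The difference in CMT technique ("Sunwoo manual therapy may cause unnecessary irritation to the area affected by breast cancer") concerns how the intervention is defined, which covariate adjustment would not settle.

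**Conclusion.** The point holds as an efficiency loss of should-fix weight; the planned test is not invalid. With equal SDs at the two visits, the stated ANOVA gives intervals that ANCOVA would narrow by 19%, 13% and 8% at correlations of 0.3, 0.5 and 0.7. With a baseline SD at 0.8 of the week-5 SD, the narrowing falls to about 11%, 6% and 1%. In the equal-SD case, at 24 per arm, pairwise power for a 0.6 SD difference is 9 to 15 percentage points lower than it could be.

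The cost of omitting cancer type depends on its link with change. It is nil if there is none and reaches about 12% excess width for a 1.0 SD gap at correlation 0.5, always on the conservative side. The correlation, SD ratio, treatment difference, stratum gap, stratum split and block size are all assumptions.

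**What to change.** In section 3.9, and in the analysis plan, replace the ANOVA by a linear model (ANCOVA) of the week-5 FACT/GOG-Ntx score, or equivalently its change, on arm, baseline score and cancer type. Report Tukey-adjusted pairwise differences with 95% confidence intervals. Use the same model, with the matching baseline, for the continuous QLQ-CIPN20 and QLQ-C30 scores. If the analysis plan already contains these terms, bring the protocol sentence into line with it.

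The cost is one amended sentence, made before unblinding. Both variables are already collected, so no new data and no further patients are needed.

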**Figure 1 F1:**
[figure not shown]
Flow chart of the trial. CMT = Chuna manual therapy, EA = electroacupuncture.

The patients visit the hospital five times for evaluation. Screening (visit 1) includes only those participants who have submitted the informed consent form. For screening, demographic information, medical history, physical examination, vital sign, questionnaire survey, laboratory test, pregnancy test (childbearing age females), neurological exam (decided by the attending physician for exclusion diagnosis purpose), and selection/exclusion criteria were be evaluated. Patients who have passed the screening test will have a 7-day run-in period, during which all medications prescribed for controlling the symptoms of peripheral neuropathy will be stopped.

Ninety patients were enrolled and randomly divided into three groups. However, if no such drugs were being used during the screening test, randomization began immediately. The visits are designed for patient evaluation at approximately 2 weeks (visit 2: baseline visit), 4 weeks (visit 3), 7 weeks (visit 4), and 11 weeks (visit 5: outpatient follow up) after the screening test. These visits include evaluation of the medical and medication history, basic physical examination, vital signs, laboratory tests, pregnancy test (for women of childbearing age), primary effectiveness and secondary effectiveness assessments, exploratory effectiveness assessment (chemotherapy completion rate: whether all planned chemotherapy procedures were performed without interruption due to CIPN), and nerve conduction study (NCS). The coordinators of the trial will inform the patient of the next visit schedule for each visit and encourage participation. The clinical trial conductor will instruct the participant to ensure compliance with the treatment. The assessment of treatment compliance with pregabalin will be based on the planned dose and the actual dose taken, as well as the quantity returned and the quantity not returned at each patient visit. The calculation is based on the actual number of treatments compared to the planned number of treatments for EA and CMT.

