### Sample size calculation

3.3

This study is a pilot clinical trial, which aims to evaluate the efficacy and safety of combined treatment with EA and CMT, compared to the conventional-therapy group (pregabalin treatment group). We determined that it would be desirable to proceed with the minimum number of participants possible, to meet the goals of this study. Moreover, earlier clinical studies involving acupuncture or EA for CIPN have included sample sizes of about 20 participants per group.^[17,18]^ Thus, we concluded that this study should include 30 participants in each group (total sample size: 90). Even if the dropout rate is assumed to be 20%, this sample size is larger than that for similar earlier studies.

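### The primary test is an unadjusted single-visit ANOVA of change: it leaves out baseline and stratum adjustment and the visit 3 score, and it needs a week-5 value that the ITT set does not require

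*Protocol article*

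**What the plan says.** Section 3.9 of the protocol article fixes the primary test: ANOVA to "test the differences between the groups for changes in FACT/GOG-NTX at the end of week 5, compared to baseline", followed by Tukey comparisons if the overall test is significant. No covariate is named.

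Section 3.2 puts baseline (visit 2) at about 2 weeks after screening and the later visits at "4 weeks (visit 3), 7 weeks (visit 4), and 11 weeks (visit 5: outpatient follow up"). Primary effectiveness is listed among the assessments at these visits, so the FACT/GOG-Ntx subscale is also scored at visit 3.

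The analysis sets are in section 3.9: "Intention-to-treat (ITT) analysis will be performed in patients who have received at least one pregabalin trial", or at least one acupuncture or CMT session. No week-5 score is required. The per-protocol set asks for one post-baseline evaluation, which could be visit 3 alone. Section 3.6 stratifies randomisation by cancer type (breast or colorectal).

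On losses, section 3.3 says only: "Even if the dropout rate is assumed to be 20%, this sample size is larger than that for similar earlier studies".

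**The concern.** The stated test and the stated analysis sets do not fit together. A change score at one visit is undefined for a patient without that visit, yet both sets admit such patients. Something further must happen to them: imputation, or exclusion in practice. The article does not say which.

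The test also leaves collected information unused. Baseline enters only as a subtraction, which is less efficient than regression on baseline unless the two scores are perfectly correlated. The stratification factor is left out. The score taken two weeks into treatment plays no part.

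At stake are precision, in a trial with only 30 per arm, and possibly bias. Participants know their arm (section 3.6). Section 3.8.5 lists use of analgesics or other neuropathic pain drugs, and compliance below 70%, as grounds for termination or dropout. Missing week-5 scores could therefore be related to outcome or to arm.

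**Working it through.** **Inputs from the article.** 30 per arm, 90 in total (section 3.3); hypothetical dropout 20% (section 3.3); two-sided 5% level (section 3.9). The article gives no SD, effect size, power or correlation, so everything below in SD units rests on assumptions.

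**The plan's own figures.** 3 × 30 = 90. With 20% dropout, 30 × 0.80 = 24 per arm (72 in total), which exceeds the roughly 20 per group of the earlier studies. The stated comparison is reproduced; there is no power calculation to reproduce.

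**Timing.** Visit 4: 7 − 2 = 5 weeks after baseline, so week 5 is visit 4. Visit 3: 4 − 2 = 2 weeks after baseline.

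**Cost of losing week-5 scores without imputation, if all dropout precedes visit 4.** The SE rises by √(30/24) = 1.118. The pairwise difference detectable with 80% power, in SDs of the change score and before the Tukey adjustment, is (1.960 + 0.842) × √(2/n): 0.72 at n = 30 and 0.81 at n = 24.

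**Precision of the contrast.** Take the SD of a single score as 1, the correlation of baseline with each later score as 0.6, the visit 3 to visit 4 correlation as 0.7, and 24 per arm with a week-5 score.
- Change score, as planned: variance 2(1 − 0.6) = 0.80, so SE = √0.80 × √(2/24) = 0.258.
- Week-5 score adjusted for baseline, same patients: variance 1 − 0.6² = 0.64, so SE = 0.80 × √(2/24) = 0.231.
- Adding visit 3, if every dropout has one: the partial correlation given baseline is (0.7 − 0.36)/0.64 = 0.53, whose square is 0.28. Effective n per arm = 1/(0.72/24 + 0.28/30) = 25.4, so SE = 0.80 × √(2/25.4) = 0.224.

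Baseline adjustment thus cuts the SE by about 11%, and visit 3 by about a further 3%. Simulated trials of 30 per arm agree: about 0.26, 0.235 and 0.23. The SE ratio from baseline adjustment is √((1 + r)/2), which is 0.87, 0.89 and 0.92 for r = 0.5, 0.6 and 0.7. The gain from the stratum cannot be sized from the article.

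**Possible bias.** With the same correlations and about 20% missing at visit 4, simulation of the analysis restricted to patients with a week-5 score gave:

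| Assumed dropout mechanism | Bias of the contrast |
|---|---|
| Control arm only, driven by the visit 3 score | 0.02–0.03 SD |
| Control arm only, driven by change from baseline to visit 3 | about 0.14 SD |
| Same rule in both arms | about 0 with no true effect; otherwise a few hundredths of an SD |

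The second row moves with how tightly dropout follows the change: about 0.095 for a looser link, 0.19 for a deterministic one. An estimate using baseline and visit 3 was essentially unbiased in scenarios where dropout depended only on those scores, that is, where data were missing at random.

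**The case against.** The strongest reply is that this is largely silence about missing data in a condensed article. A reader might infer that the plan drops every patient without visit 4. No section says so. ANOVA can be run on imputed values, and the full protocol or an SAP, neither shown, may hold a rule. That reply stands, and the shrinkage to 24 per arm is conditional on there being no such rule.

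A reader might also infer that about 6 of 30 per arm will lack the primary score. The 20% is a hypothetical figure for the whole study. Losses between visits 4 and 5 leave the week-5 score intact, and section 3.8.5 does not say that assessments end when treatment does. So 24 per arm is the worst case under that figure.

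A third tempting reading is that the control arm will be flattered because its poor responders leave. Nothing in the article establishes this. EA involves 3 × 2 + 2 × 3 = 12 sessions and CMT 2 × 2 + 1 × 3 = 7, so low compliance could equally fall in the add-on arms. Dropout confined to poorly responding controls would bias against the add-on therapies, not for them. Neither direction nor size can be asserted.

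Finally, ANOVA of change at a pre-specified visit is valid and common, and section 3.3 calls the trial a pilot. This limits the severity. It does not answer the point about method: an imputation rule would still leave the stated test without baseline adjustment, without the stratum and, for patients who attend visit 4, without visit 3.

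**Conclusion.** The point holds as a weakness of the method that is stated. The unadjusted ANOVA of week-5 change omits the baseline covariate, the stratification factor and the visit 3 score, and it requires a value that neither analysis set requires.

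The firmest part is precision: an SE of about 0.26 SD against about 0.23 SD, under assumed correlations of 0.6 to 0.7, with most of the gain from baseline adjustment and little from visit 3. Bias from differential dropout is possible but depends on the mechanism, at about 0 to 0.14 SD in the assumed scenarios. The reduction of the ITT analysis to patients with a week-5 score follows only if no missing-data rule exists elsewhere. The change is worth making because it is cheap; the planned test is not invalid.

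**What to change.** Make the primary analysis a mixed model for repeated measures of the post-baseline FACT/GOG-Ntx scores, with arm, visit, arm-by-visit, baseline score, baseline-by-visit and cancer stratum. Take the arm contrasts at visit 4 (week 5) as primary, and keep the Tukey step for the pairwise comparisons. With baseline in the model, the visit 4 contrast still estimates the difference in mean change at week 5, so the primary outcome is unchanged. Keep the planned ANOVA as a sensitivity analysis.

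The cost is revised analysis wording and a little more programming; no new data are needed. The model relies on a missing-at-random assumption, which should be stated. It also recovers nothing for a patient with no post-baseline score, so the number of such patients should be reported by arm.

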## Objective

2

The study aims to verify the hypothesis that the concurrent use of CMT or acupuncture treatment with pregabalin, a medication commonly used for CIPN is more effective and safe for the relief of CIPN symptoms than is pregabalin-alone therapy.

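### The two comparisons with pregabalin alone are made conditional on a three-group F-test and adjusted for a third pair that is not an objective: valid, but inefficient for the trial's own question

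*Protocol article*

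**What the plan says.** Under Statistical analysis (3.9), the article states "Primary outcome assessments are performed with ANOVA analysis to test the differences between the groups" for the change in FACT/GOG-NTX from baseline to the end of week 5. The next sentence is the pairwise rule: "If the differences between groups are significant, the Tukey method will be used". On error level and intervals it says only "All statistical tests will be performed as two-sided tests with a significance level of 5%, and two-sided 95% confidence intervals", without naming a contrast.

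Under Objective (2), the hypothesis is that adding CMT or acupuncture to pregabalin "is more effective and safe for the relief of CIPN symptoms than is pregabalin-alone therapy". The last paragraph of the Introduction and Sample size calculation (3.3) name the same comparator, pregabalin alone. No section states EA v CMT as an aim.

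Sample size calculation also says "This study is a pilot clinical trial". It plans 30 per group and 90 in total, allows for 20% dropout, and gives no effect size, SD or power.

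**The concern.** The objective needs two contrasts that share one control. The stated analysis differs from that in three ways.

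- The F-test asks whether any of the three means differ. It can be significant because of EA v CMT alone, so it does not answer the objective.
- Tukey's method adjusts for all three pairs, so part of the 5% is spent on EA v CMT.
- The pairwise step depends on a significant F. Tukey's method already controls the family-wise error over all pairs without a preliminary test, so the gate adds nothing to error control.

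At stake are some power on the two contrasts of interest, and whether the contrasts with control are reported when the F-test is not significant. Those estimates are the most useful product of a pilot.

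**Working it through.** **The plan's own figures.** 3 × 30 = 90, and 30 × (1 − 0.20) = 24, which exceeds the roughly 20 per group of the earlier studies. Both statements reproduce. No power figure is given to reproduce.

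**Inputs.** From the article: three groups, 1:1:1, n = 30 or 24 per group, two-sided 5%, one-way ANOVA on change, Tukey only after a significant F. Assumed: normal data with equal variance, and effects of 0.5, 0.6 and 0.8 SD.

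**Critical values at n = 30 (df = 3 × 30 − 3 = 87).** Each control contrast has t = (mean of arm − mean of control) / (s√(2/n)).

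- F gate: F(0.95; 2, 87) = 3.101.
- Tukey, three pairs: |t| > q(0.95; 3, 87)/√2 = 2.384.
- Dunnett, two contrasts with correlation 0.5: |t| > 2.249.
- Simultaneous 95% CI half-width, c√(2/30) = c × 0.2582: Tukey 2.384 × 0.2582 = 0.616 SD; Dunnett 2.249 × 0.2582 = 0.581 SD.

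**Error under the global null (simulation, n = 30).**

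- All three pairs: 5.0% with Tukey alone, 4.5% with gate plus Tukey.
- The two control contrasts: 3.25% as written, 3.6% with ungated Tukey, 5.0% with Dunnett.

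**Power for the effective arm v control (only that arm effective), and how often the gate stays closed.**

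| n per arm | Assumed effect | As written | Tukey, no gate | Dunnett | Cost of gate | Cost of third pair | F not significant |
|---|---|---|---|---|---|---|---|
| 30 | 0.5 SD | 32.4% | 33.2% | 38.1% | 0.8 | 4.9 | 51% |
| 30 | 0.6 SD | 47.3% | 48.0% | 53.3% | 0.7 | 5.3 | 35% |
| 30 | 0.8 SD | 75.8% | 76.1% | 80.1% | 0.3 | 4.0 | 11% |
| 24 | 0.5 SD | 25.3% | 26.1% | 30.5% | 0.8 | 4.4 | 60% |
| 24 | 0.8 SD | 64.2% | 64.6% | 69.5% | 0.4 | 4.9 | 19% |

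The cost columns are differences in percentage points: (Tukey, no gate) − (as written), and Dunnett − (Tukey, no gate). With 24 per arm and 0.6 SD in one arm, the gate stays closed in 45% of trials.

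With both arms effective at 0.6 SD and n = 30, the chance of at least one significant control contrast is 62.8% as written and 69.5% with Dunnett. The gate accounts for about 1.3 of those 6.7 points.

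**What a closed gate hides.** At n = 30 with 0.6 SD in one arm, the gate is closed while Dunnett is significant for that arm in 2.4% of all trials. That is 2.4/35, or about 7% of the closed-gate trials. With both arms at 0.6 SD, the gate is closed while at least one control contrast is Dunnett-significant in about 5% of all trials.

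**The case against.** The rule is valid. Family-wise error is controlled, and all-pairs testing is a conventional choice with two active add-on arms. A reader might infer from the gate followed by Tukey that false positives are inflated. The opposite is true: the rule is conservative. This objection stands.

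A reader might also take the redundant gate for the main harm. The table does not support that. The gate costs under 2 points, and most of the loss is the price of the third pair.

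The 35% and 45% are likewise not lost findings. In about 93% of the closed-gate trials at 0.6 SD in one arm (n = 30), Dunnett would not have found the effective arm's contrast significant either. The closed gate mostly reflects low power.

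Finally, a reader might conclude that the plan forbids effect sizes and confidence intervals when F is not significant. That is too absolute. The article mentions two-sided 95% CIs in general terms and descriptive summaries by visit, and the Tukey sentence governs a test, not every estimate. Nor is it a fault that a condensed article does not list every table.

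What the objection does not remove is the rule itself. The article fixes both the pairwise method and its trigger, and ties neither the CIs nor the summaries to the two contrasts in the objective. An analysis plan that always reported those contrasts with an adjustment for two comparisons would change this rule, not merely fill in a detail.

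**Conclusion.** The point holds as one of efficiency and conditional reporting, not of validity. For the two contrasts in the objective, the written rule uses about 3.2% of the allowed 5% and gives up roughly 4 to 7 percentage points of power against Dunnett. Nearly all of this is due to adjusting for EA v CMT. The CI half-width at 30 per arm is 0.616 SD instead of 0.581 SD. As worded, the only stated pairwise step is not reached in about 35% (n = 30) or 45% (n = 24) of trials with a 0.6 SD effect in one arm.

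The critical values, half-widths and null error rates need no effect size. The power and closed-gate figures rest on assumed effects and on normal data with equal variance. This is a cheap improvement.

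**What to change.** Name EA + pregabalin v pregabalin and CMT + pregabalin v pregabalin as the primary contrasts. Estimate both from the planned ANOVA model, with Dunnett-adjusted p-values and simultaneous 95% CIs, and report them whatever the omnibus result. Keep the F-test as descriptive, and give EA v CMT as an exploratory estimate.

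This changes analysis wording only: no further patients, visits or data, and no change of model. The one downside is that EA v CMT, which is not an objective, loses formal multiplicity-controlled testing.
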